**Recruitment/Timeline (fig 3)**

We anticipate recruiting over 2.5 yrs (fall 2016-spring 2019). Total timeline for the trial is 5 yrs, to ensure follow-up of all recruited women for 2 yrs postop. The main centre in Vancouver (2 surgeons) is committed to recruiting 1-2 patients per week or 130 total. Edmonton (1 surgeon), Calgary (1 surgeon) and Montreal (2 surgeons) would recruit 76 patients each. Based on prior experience with the pilot study of BSSVF-M and OPTIMAL, we anticipate approximately 90% of invited women will volunteer and 5% of those will change their mind about participation at baseline. ^13^ Given the NPA performs 4 to 8 vaginal surgeries for POP per month, we anticipate no recruitment challenges. Based on surgical volumes and commitment to research, the other sites should also reach targets. All surgeons are experts at vaginal surgery for POP (including SSLS) and all except one have performed BSSVF-M. They do not currently offer BSSVF-M outside research studies. According to national credentialing organizations^9^ and our surgical survey, surgeons require at least 5 and on average 8 procedures to become familiar with a new vaginal POP technique. Assistance with 8 cases will be provided to the surgeon untrained to perform BSSVF-M. In addition, video instruction will be provided to standardize procedure and materials.

**Challenges/Mitigation**

Compliance problems

Compliance with follow-up may be an issue due to the follow up for 2 years. Patients will be screened for future compliance at recruitment and the coordinator at each site will follow each patient quarterly over the 2 years, asking for updated contact information at each time point.

Loss to follow-up

We anticipate similarities in loss to follow-up (15%) to OPTIMAL. To mitigate loss to follow-up, we will reimburse patient parking and traveling costs with a small stipend.

Unblinding of participants

In the event of complications arising from either surgery, patients or assessors may become aware of the group assignment. For example, if a patient develops exposure of the vaginal mesh, the pelvic examination will reveal this at various time points and surgery may be needed to remove the mesh exposed in the vagina. This may introduce bias in assessments at various time points, however it will likely not affect the primary composite outcome measure at 2 years. Based on our prior experience with BSSVF-M, we anticipate unblinding complications to be less than 5% of the total sample. The primary surgeon who deals with complications and need for reoperation is not involved in pelvic examination assessments. Most complications will be corrected by 2 years, so the blinded assessor at 2 years will be unable to identify group assignment.

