Change in maximal POP of vaginal compartments via POPQ, obtained by research personnel (nurse or clinical fellow) trained in POPQ and blinded to group allocation. POP will be quantified and compared to baseline. Numerical questionnaire scores will be compared between the two groups from baseline to 6 weeks, 12 and 24 months postoperatively. Change in questionnaire scores between the 2 groups from baseline to 6 weeks, 12 and 24 months postoperatively: Pelvic Floor Distress Inventory (PFDI-20) and the Pelvic Floor Impact Questionnaire (PFIQ-7)^17^; the short form McGill pain questionnaire^18^; a validated gender-specific body image scale specifically for POP.^8^ Change in questionnaire scores between the 2 groups from baseline to 12 and 24 months: Pelvic organ prolapse/ Incontinence Sexual Questionnaire, IUGA-Revised (PISQ-IR)^19^. Difference between global impression of improvement (Likert Scale) of the 2 groups at 6 weeks, 12 and 24 months postoperatively. Difference between the 2 groups in length of surgery, postoperative hospital stay, complications such as pain or mesh exposure, reoperations and other unexpected adverse events categorized using the Clavien Dindo validated classification system for surgical complications.^20^ Difference in health utilities measured via the EuroQol instrument (EQ-5D)^21,22^ and in direct healthcare utilization and costs collected by the healthcare service utilization questionnaire^23^ at baseline, 6 weeks, 6, 12 and 24 months postoperatively.

Health economic evaluation

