| Questionnaires:  Self-reported Charlson Comorbidity Index  Pelvic Floor Distress Inventory – 20 (PFDI-20)  Pelvic Floor Impact Questionnaire – 7 (PFIQ-7)  Pelvic organ prolapse/Incontinence Sexual Questionnaire (PISQ-IR)  The short form McGill Pain Questionnaire (McGill PQ)  The Body Image in Pelvic Organ Prolapse Questionnaire (BIPOP)  EQ-5D-3L Questionnaire (within the last 6 months)  Healthcare service utilization questionnaire (within the last 6 months) | | | | |
| OR details | | **INTRAOP** | | OR details |
| 6 week POP Quantification  Clavien Dindo complication scale | | **POSTOP** | | 6 week POP Quantification  Clavien Dindo complication scale |
| Questionnaires:  PFDI-20  PFIQ-7  McGill PQ  BIPOP  Global Question of Improvement  EQ-5D-3L  Healthcare service utilization questionnaire | | | | |
| 6 month phone call | | **PHONE EVALUATION** | | 6 month phone call |
| Questionnaires:  EQ-5D-3L  Health care service utilization questionnaire | | | | |
| 12 month questionnaires  POP Quantification  Clavien Dindo complication scale | | **MID-TRIAL ASSESSMENT** | | 12 month questionnaires  POP Quantification  Clavien Dindo complication scale |
| Questionnaires:  PFDI-20  PFIQ-7  PISQ-IR  McGill PQ  BIPOP  Global Question of Improvement  EQ-5D-3L  Healthcare service utilization questionnaire | | | | |
| 24 month questionnaires  POP Quantification  Clavien Dindo complication scale | | **FINAL ASSESSMENT** | | 24 month questionnaires  POP Quantification  Clavien Dindo complication scale |
| Questionnaires:  PFDI-20  PFIQ-7  PISQ-IR  McGill PQ  BIPOP  Global Question of Improvement  EQ-5D-3L  Healthcare service utilization questionnaire | | | | |

**Figure 2:** **Vault suspension techniques:** a) **BSSVF-M**^13^ – novel technique performed with bilateral synthetic mesh arms attached to sacrospinous ligaments to replace the vagina tension-free in its normal anatomic orientation within the pelvis, can carry risks of mesh exposure and pain; b) **SSLS** - standard technique mostly performed with unilateral (but can be bilateral) synthetic sutures attached to sacrospinous ligaments, tensioned and anatomically incorrect, can carry risks of pain, detachment and prolapse recurrence.

[figure not shown]

[figure not shown]

1. Bilateral Sacrospinous Vault Fixation b) Unilateral Sacrospinous Ligament

with **Mesh arms (BSSVF-M)^13^** Suspension with **synthetic sutures (SSLS)**

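### The protocol's claim that the 2-year examiner cannot identify the arm does not follow from its own text, so the POP-Q part of the primary endpoint carries an unprotected risk of examiner bias

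*Protocol*

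**What the plan says.** The Challenges/Mitigation section (Unblinding of participants) says that after complications of either operation "patients or assessors may become aware of the group assignment". Its example is mesh exposure: "if a patient develops exposure of the vaginal mesh, the pelvic examination will reveal this at various time points". It allows that this may bias assessments but expects the 2-year primary outcome to be largely unaffected. It gives three reasons:

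- Frequency: "we anticipate unblinding complications to be less than 5% of the total sample".
- Separation of roles: "The primary surgeon who deals with complications and need for reoperation is not involved in pelvic examination assessments".
- Timing: "Most complications will be corrected by 2 years, so the blinded assessor at 2 years will be unable to identify group assignment".

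Elsewhere, Outcome measures says that POP-Q is "obtained by research personnel (nurse or clinical fellow) trained in POPQ and blinded to group allocation". Interventions and Allocation also state that outcome examiners are blinded. Figure 1 places POP-Q and the "Clavien Dindo complication scale" together at 6 weeks, 12 months and 24 months.

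Under Outcome measures, two of the four failure components are POP-Q readings (apical descent, and anterior or posterior wall descent). Under Sample size, a woman who misses the 2-year visit but was a failure when last seen counts as a failure.

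**The concern.** The timing argument treats blinding as a matter of what can be seen on the day. Blinding concerns what the examiner knows. An examiner who saw an exposure at 12 months still knows the arm at 24 months, whether or not it has been repaired. The conclusion needs a 2-year examiner who has not examined the woman before and who does not learn her complication history at the visit. The protocol requires neither.

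The two anatomic components are readings in centimetres judged against a cut-off, so knowledge of the arm could tip a borderline reading. Mesh exposure is the only unblinding complication that the protocol names, and Figure 2 lists it as a risk of BSSVF-M alone. Any effect would therefore fall unevenly on the arms, and randomisation does not balance it.

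**Working it through.** **The logic, set against the text**

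1. The stated premise is that most complications are corrected by 2 years. The stated conclusion is that the examiner is unable to identify the arm. *Most* is not all, so some exposures may still be visible at the 24-month examination.
2. The same paragraph says that the examination itself shows the exposure at various time points. Later repair does not undo that knowledge.
3. The one named separation keeps the primary surgeon out of the examinations. It does not concern a nurse or fellow who examined the woman at 6 weeks or 12 months.
4. Figure 1 names neither the person nor the order for POP-Q and Clavien Dindo. A past exposure could be discussed before the primary-endpoint reading is taken.
5. The Sample size rule lets a failure at an earlier visit become the primary result. For a woman who then misses the 2-year visit, later repair cannot protect that reading.

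**The plan's own figure**

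Inputs (Sample size): success 60% v 75%, two-sided alpha 0.05, power 80%, 15% loss.

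n = [1.960·√(2·0.675·0.325) + 0.842·√(0.60·0.40 + 0.75·0.25)]² / 0.15² = 151.9, so 152 per group. Then 152/0.85 = 178.8, so 179. Both figures reproduce, and power at 152 per group is 80.0%. The sample size is not at issue.

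**How many women**

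5% × 358 = 17.9, about 18. If all are in BSSVF-M, 17.9/179 = 10% of that arm. In the evaluable set, 5% × 304 = 15.2, and 15.2/152 is again 10%. The protocol says less than 5%, so this is a ceiling.

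**What misrating could do**

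Assumption, not in the documents: a fraction m of the affected women are misrated, and SSLS is unaffected. All results use the two-sided z test with 152 per group.

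(a) True rates 60% v 75%, true successes rated as failures: observed BSSVF-M success = 0.75 × (1 − 0.10·m).

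| m | BSSVF-M success | Loss (points) | Power |
|---|---|---|---|
| 10% | 74.25% | 0.75 | 76% |
| 25% | 73.1% | 1.9 | 68% |
| 50% | 71.25% | 3.75 | 54% |

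(b) Same true rates, true failures rated as successes: 0.75 + 0.25 × 0.10·m. For m = 10%, 25% and 50%, success is 75.25%, 75.6% and 76.25%, and power is 81%, 83% and 86%.

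(c) No true difference (60% in both arms), true failures rated as successes: 0.60 + 0.40 × 0.10·m. For m = 10% to 50%, success is 60.4% to 62.0%, and two-sided error is 5.1% to 6.5%. The most that can move upward is 0.40 × 10% = 4 points.

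(d) No true difference, true successes rated as failures: 0.60 × (1 − 0.10·m). For m = 10% to 50%, success is 59.4% to 57.0%, and two-sided error is 5.1% to 8.3%.

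**The case against.** The best defence is that the sentence is loosely worded but the exposure is small. The protocol expects unblinding in fewer than 5% of women, counts patients as well as examiners within that figure, declares outcome examiners blinded in several places, keeps the surgeon away from the examinations, and says only that the primary outcome will *likely* be unaffected. Visit order and rostering are often set in site procedures. All of this limits the size. None of it supports the statement that the examiner will be unable to identify the arm, because blinding is declared as a status and the same paragraph concedes that it can be lost.

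The documents do not support four stronger readings that a reader might infer:

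- *That the result will be biased, for or against BSSVF-M.* Nothing shows that any reading would change, and the direction is not determined.
- *That the same examiner sees each woman throughout, or also grades complications.* The protocol leaves both open. It gives no size for the examiner pool.
- *That an exposure always identifies the mesh arm.* Eligibility allows a synthetic anti-incontinence sling in either arm. A tilt towards BSSVF-M is plausible but not certain.
- *That a false-positive rate near 15% is in reach.* An upward shift from 60% to 65% would give 14.6%, but only 4 points can move upward. A 5-point downward shift would need 83% of the true successes among the affected women to be misrated (5 points out of 0.60 × 10% = 6).

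The figures in the working are themselves upper-end. They put the whole 5% on examiners and on one arm. A woman who fails on bulge symptoms or re-treatment also cannot be made a success by a POP-Q reading.

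**Conclusion.** The point holds as a gap in protection. The protocol states that blinding is secure at the primary assessment, and its own text does not support that. The readings at risk feed two of the four primary components, at 2 years and, through the carried-forward failure rule, at earlier visits.

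The size is small to moderate: at most about 18 women. On the assumption of 10-50% misrating in one direction and all affected women in BSSVF-M, power runs from 76% down to 54% if true successes are marked down. With no true difference, error is 5.1-6.5% if true failures are marked up. The misrating fraction has no source in the documents. What justifies a change is the low cost of prevention and measurement, not evidence that bias has occurred. A later analysis plan could add the sensitivity analysis, but it could not recover examiner awareness that was never recorded at the visit.

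**What to change.** 1. In Challenges/Mitigation, replace the inference with a statement that repair of a complication does not restore an examiner's blinding.
2. At each in-person visit, measure and lock POP-Q before any complication history or Clavien Dindo grading is taken. Do not show the examiner the earlier complication record.
3. Straight after POP-Q, the examiner ticks whether they know or have seen anything that identifies the arm. This is done for every woman in both arms.
4. Repeat the primary comparison with the anatomic components of flagged women set first to failure and then to success.

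Two tempting additions should be avoided. Giving Clavien Dindo to the site coordinator would pass a secondary outcome to the person who performs the randomisation, and the protocol does not say that this person is blind to the result. Changing the examiner only for women with a recorded exposure could itself signal the arm.

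The cost is one form field, a fixed visit order and one extra analysis, with no added staff or visits. The order cannot help when the examination itself shows the exposure, which is why the flag and the sensitivity analysis are needed as well.

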**Sample size**

179 women/group (358 total). Our Western Canadian survey of 50 surgeons indicated the smallest clinically relevant difference to change surgical practice would be an absolute change of 14%. The proportion of success in the control SSLS group was 60.5% in the OPTIMAL trial^4^ and the success rate with BSSVF-M was 77% in our one-year pilot study.^13^ Our pilot study was small and designed to inform a power calculation for an RCT; it did not study long-term results, cost effectiveness or KT strategies. Studies of mesh vs sutures in surgery for urinary incontinence indicate that mesh is more successful, durable and cost-effective than sutures,^26-29^ therefore we expect similar results for POP, with sustained durability of mesh over time. Our primary analytic strategy, following the example of the OPTIMAL trial, will include only patients who come for 2-yr follow-up or who were failures on the last follow-up. Patients who do not come to their 2-yr follow-up but who were failures at last follow-up will be counted as failures. Sample size was determined based on a two-sample test of independent proportions, using two-sided ∝=0.05, anticipated successful outcome rates 60 and 75%, power=80% and yielded 152 patients/group. To account for an estimated 15% loss to follow-up (patients who never had a follow-up visit or who were deemed successful on their last follow-up), similar to the OPTIMAL trial, our sample size was increased to 179 per group.

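### The primary analysis keeps 2-year non-attenders last seen as failures but drops those last seen as successes, so inclusion depends on outcome

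*Protocol*

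**What the plan says.** The Primary Objective is a comparison of the two operations on the composite outcome at 2 years. The analysis rule stands in the protocol's Sample size section. The primary analysis "will include only patients who come for 2-yr follow-up or who were failures on the last follow-up". The section then adds: "Patients who do not come to their 2-yr follow-up but who were failures at last follow-up will be counted as failures". The women left out are those who form the allowance for loss, described as "15% loss to follow-up (patients who never had a follow-up visit or who were deemed successful on their last follow-up". The only reason given is that the OPTIMAL trial did the same.

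Only the protocol is at hand. A statistical analysis plan may add sensitivity analyses, but the protocol itself names this rule as the primary strategy.

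**The concern.** Take two women who both miss the 2-year visit. The one last seen as a failure stays in the denominator, and the one last seen as a success is removed. Excluding both would be unbiased if missingness were unrelated to outcome, and carrying the last status forward would at least treat both alike. This rule does neither, so an arm's success rate can be wrong even when attendance is completely random.

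The same history can also be scored two ways. A woman who fails at 12 months without re-treatment, and would meet the success definition at 24 months, is a success if she attends and a failure if she does not.

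At stake are both reported success rates and, if attendance differs between arms, the difference between them and the type I error of its test.

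**Working it through.** **Inputs from the protocol (Sample size).** The calculation uses "two-sided ∝=0.05" and "anticipated successful outcome rates 60 and 75%, power=80% and yielded 152 patients/group". The loss allowance is 15%, giving 179 per group.

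**Inputs assumed, because the protocol does not give them.**
- *m*: the probability of missing the 2-year visit, by arm, unrelated to outcome.
- *s*: the share of 2-year failures already recorded at the last visit attended.
- A woman recorded as a failure is still a failure at 2 years.
- The true success rates *p* are 60% (SSLS) and 75% (BSSVF-M).

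**Step 1: the plan's own figures.** Two-proportion formula with pooled variance and no continuity correction:

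n = [1.960 × √(2 × 0.675 × 0.325) + 0.842 × √(0.60 × 0.40 + 0.75 × 0.25)]² / 0.15² = 151.9, so 152.

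152 / 0.85 = 178.8, so 179. Both stated figures reproduce.

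**Step 2: expected success under the rule.** The analysed set is all attenders, (1 − m), plus the non-attenders already recorded as failures, m·s·(1 − p). Only attenders can be successes. Hence

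observed success = p(1 − m) / [(1 − m) + m·s·(1 − p)].

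With s = 0 this returns p. With s > 0 and m > 0 it is below p.

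**Step 3: equal random non-attendance, m = 15%.**
- s = 0.5: SSLS 0.51 / 0.88 = 58.0%; BSSVF-M 0.6375 / 0.86875 = 73.4%; difference 15.4 points.
- s = 1: SSLS 0.51 / 0.91 = 56.0%; BSSVF-M 0.6375 / 0.8875 = 71.8%; difference 15.8 points.

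The difference is overstated by about 0.4 to 0.8 points. If both arms truly have 60% success, with equal m and s, the two expected rates are identical and the bias in the difference is zero. Simulated type I error (200,000 trials, 179 per arm, s = 0.75) was 5.0%.

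**Step 4: unequal non-attendance, s = 1.**

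| True SSLS / BSSVF-M | Missed SSLS / BSSVF-M | Observed SSLS | Observed BSSVF-M | Difference |
|---|---|---|---|---|
| 60 / 75 | 20% / 10% | 0.48 / 0.88 = 54.5% | 0.675 / 0.925 = 73.0% | 18.4 |
| 60 / 75 | 10% / 20% | 0.54 / 0.94 = 57.4% | 0.60 / 0.85 = 70.6% | 13.1 |
| 60 / 60 | 20% / 10% | 0.48 / 0.88 = 54.5% | 0.54 / 0.94 = 57.4% | 2.9 |

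For the last row the simulated type I error was 8.4%. With s = 0.75 the spurious difference was about 2.3 points and the type I error 7.0%.

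**Step 5: when the direction reverses.** Suppose that 60 of 100 women are true successes, and that 15 of the 40 failures were last seen as successes and stay away because they later failed. All 15 are dropped, and the analysed rate is 60 / 85 = 70.6%, which is too high. This is an extreme case, chosen to show the sign.

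**The case against.** The strongest reply is that the effect on the treatment comparison is small in the situation the plan expects. Patients are blinded, sites contact them quarterly and travel costs are reimbursed, all of which makes a wide gap in attendance less likely. Step 3 bears this out: under a point with balanced dropout, and nothing under a true null. Counting an earlier failure as a failure is also reasonable in itself, above all for re-treatment, which is already a component of the endpoint. And the 60% planning rate is taken from OPTIMAL, whose strategy the protocol says it follows, so that rate may already be on the rule's own scale. These points stand. They limit the size of the problem but do not justify pairing retained failures with excluded successes.

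Several stronger readings are tempting, and the protocol does not support them:
- *The rule always lowers the success rates.* Step 5 shows that it need not.
- *The arm with poorer attendance always moves more.* With s = 1, 22% missing in a 75% arm gives 0.585 / 0.835 = 70.1%, a fall of 4.9 points. Only 20% missing in a 60% arm gives 54.5%, a fall of 5.5.
- *Type I error is inflated whatever happens.* Under the model above, that needs attendance or timing of failure to differ between arms, and the protocol gives no such figures.
- *The rule contradicts the Challenges/Mitigation section*, which says of bias from unblinding that "it will likely not affect the primary composite outcome measure at 2 years". That is a statement of likelihood, with unblinding complications put below 5% of the sample. A woman would have to be unblinded, miss the 2-year visit and be a failure at her last visit. If the first two are independent with 20% non-attendance, they coincide in fewer than 5% × 20% = 1% of women, before the third condition.
- *The 15% allowance inflates any true difference by 1 / 0.85.* That requires every excluded woman to be a true 2-year success. The excluded group also contains women never seen, and a woman last seen as a success may fail later.
- *The reported difference is on another scale than the 14 points named by the surveyed surgeons.* The protocol does not say how missed visits were put to them.

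**Conclusion.** The concern holds in a limited form and should be fixed. The protocol sets as primary a rule under which inclusion of non-attenders depends on their recorded outcome. Both success rates are biased downward if some failures are recorded before dropout and missingness depends at most on last observed status. The bias may be upward if women last seen as successes stay away because they later fail.

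For the difference, the size turns on two quantities that the protocol does not give. It is modest under balanced random dropout, and zero when true rates, attendance and timing of failure are all equal. With a 10-point gap in attendance and all failures already recorded, the rule distorts the difference by about 2 to 3.5 points in either direction and raises the type I error to about 8%. Those are illustrations under stated assumptions, not predictions for this trial. The sample size arithmetic is correct and unaffected.

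**What to change.** Make the primary analysis all randomised women by assigned arm. Keep re-treatment before 2 years as failure, as the endpoint already has it. Treat every other woman without a 2-year assessment in the same way whatever her last status, for example by multiple imputation of the 2-year composite within arm from last observed composite status, surgeon and baseline POP-Q. When missingness is unrelated to outcome, handling both kinds of non-attender alike returns the expected rates to 60% and 75%. Imputation of this kind assumes that missingness is explained by the variables used, so it does not by itself remove the reversal in Step 5.

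Keep the present rule as a sensitivity analysis, for comparability with OPTIMAL.

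The cost is a change of wording and some additional programming, with no new data and no change to 179 per group. The downside is a headline success rate less directly comparable with OPTIMAL, which the retained sensitivity analysis covers.
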